## 7.2 Secondary endpoints

　Secondary endpoint: other ultrasound findings

The ultrasound imaging described above will be performed by a blinded researcher ([name]) who will not be informed which intervention the subject has received.

# 8. observations and tests

Observation, examination and reporting schedule (Group M, Group P, Group C)

| Occasion  Inspection, observation and investigation items | Pre | Before | After |
| --- | --- | --- | --- |
|  |  |  |  |
| Obtaining consent | ● |  |  |
| Subject background (age, medical history) | ● |  |  |
| Physical examination (height and weight) | ● |  |  |
| Ultrasound images |  | ● | ● |
| Adverse events | ←△→ | | |

# 9. handling of adverse events

As this is a non-invasive interventional study, no adverse events are expected.

# 10. target number of people to be registered

　Target number of patients enrolled: 60 (20 in group M, 20 in group P and 20 in group C)

　　Enrolment period: from the date of Ethics Committee approval to 31 January 2024, depending on the subject.

　Duration of the study:from the date of approval by the Ethics Committee to 31 March 2024

# 11. statistical matters

## 11.1 Basis for setting the target number of people to be registered

To examine the changes before and after the intervention between the three different groups. The rationale for the number of subjects in each group will be based on sample size calculations. Specifically, a two-way analysis of variance will be used for statistical analysis. The number of levels is 1 (before or after the intervention) and the number of groups is 3. Assuming an effect size of 0.4, a significance level of less than 5% and a power of 0.8, the sample size for each group will be calculated to be 52 participants in total. Assuming that there will be a certain number of subjects who declare that they cannot consent to randomisation and who meet the exclusion criteria, we aim to enroll 60 subjects.

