## 11.3 Analysis items and methods

　A summary of the statistical analysis is given below. The significance level of the test is set at two-sided 0.05. For details, [name], who is responsible for the statistical analysis, will prepare the first version of the statistical analysis plan before the first patient is enrolled (first patient in), and if necessary, the second version will be fixed before the data are fixed. If a second version is prepared, it will include a history of changes from the first version.

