### 11.3.2 Hypothesis-testing analysis of primary endpoints

To determine and compare the effects on the tissues surrounding the knee joint before and after the intervention, we will compare the average of each index between the three groups.

If the p-value of this test is less than 0.05 and the mean value of each indicator after the intervention is higher in group M or P than in group C, we judge that the intervention may be useful.

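### The primary analysis is a before/after-by-group ANOVA with no stated participant term, baseline covariate or single tested effect; baseline-adjusted ANCOVA would settle this and generally gain power at no data cost

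*Protocol*

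**What the plan says.** Section 11.1 sets the aim as comparing pre-to-post change across three arms and names the method: "Specifically, a two-way analysis of variance will be used for statistical analysis". It describes the layout as "The number of levels is 1 (before or after the intervention) and the number of groups is 3" and sizes the trial by "Assuming an effect size of 0.4, a significance level of less than 5% and a power of 0.8", so that "the sample size for each group will be calculated to be 52 participants in total". Section 10 sets enrolment at 60, 20 per arm.

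Section 11.3.2 describes the primary test: "we will compare the average of each index between the three groups". It then judges an intervention possibly useful if that test gives p below 0.05 and the post-intervention mean is higher in group M or P than in group C. Section 11.3 adds: "The significance level of the test is set at two-sided 0.05".

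The schedule in section 8 has a row "Ultrasound images" marked once before and once after the intervention. Section 11.2(b) removes from the analysis anyone lacking either scan, so every analysed subject has a baseline value. Section 11.3 calls the text a summary and leaves details to a statistical analysis plan that is not shown.

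**The concern.** The two scans come from the same knee of the same person minutes apart, so they are correlated. A before/after-by-group ANOVA gives a valid p-value only if the model accounts for the pairing, and it answers the trial's question only if the right row of the table is read. The protocol settles neither. Its wording points to three different tests:

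- change between groups (the aim in 11.1), which is the group-by-time interaction;
- the average of each index between groups (11.3.2), which in a two-way table would be the group main effect;
- the mean after the intervention (the decision rule in 11.3.2), which is a post-only comparison.

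These differ in power and, if pairing is left out, in error rate. One p-value decides the trial's conclusion, so its source should not be open to choice. Even the most favourable reading uses the baseline scan less efficiently than adjusting for it.

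**Working it through.** **Inputs.** From the protocol: three groups, 20 per arm (N = 60), effect size 0.4, alpha 0.05 two-sided, power 0.8, calculated N = 52. Assumed: 0.4 is Cohen's f; normal data; equal SD (set to 1) before and after; r from 0 to 0.7, because no value is given.

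**1. The plan's own figure.** Noncentral F with independent observations, λ = N·f², denominator df = N − 3.

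- Numerator df 1, N = 52: λ = 52 × 0.16 = 8.32, power 0.807. The stated 52 reproduces.
- Numerator df 2 (needed to compare three groups): power 0.707 at 52 and 0.776 at 60; N = 64 for 80%.
- Repeated-measures interaction with f = 0.4 as the size of the interaction itself, λ = N·f²·2/(1 − r): N = 34, 25, 19, 13 at r = 0, 0.3, 0.5, 0.7. None gives 52.
- Repeated-measures between-group effect: 49 at r = 0.5 and 55 at r = 0.7, so 52 would need an unstated r in between.

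The 52 therefore fits a formula that uses no within-person correlation. That shows how N was obtained, not how the data will be analysed.

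**2. Type I error if pairing is left out.** With 120 scans treated as independent, the error df is 120 − 6 = 114 and the critical F(2,114) is 3.08. Under the null the group mean square has expectation 1 + r, the interaction mean square 1 − r, and the pooled error mean square 1. The group F is therefore too large and the interaction F too small.

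| r | Group effect | Group-by-time |
|---|---|---|
| 0 | 5.0% | 5.0% |
| 0.3 | 9.9% | 1.5% |
| 0.5 | 13.5% | 0.3% |
| 0.7 | 17.1% | 0.01% |

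These come from averaging the tail probability exp(−3.08·MSE/(1 ± r)) over the distribution of the error mean square (MSE). Simulation of 40,000 trials per setting agrees to within 0.3 percentage points.

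**3. Power of valid tests at N = 60.** Here f = 0.4 is the spread of the post-intervention means in SD units, with no baseline difference, so N·f² = 60 × 0.16 = 9.6. Numerator df is 2.

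- Mean of both scans (group main effect): effect halved, variance (1 + r)/2, so λ = 9.6/[2(1 + r)].
- Change score (equal to the repeated-measures interaction): variance 2(1 − r), so λ = 9.6/[2(1 − r)].
- Post-only: λ = 9.6.
- ANCOVA: residual variance 1 − r², so λ = 9.6/(1 − r²), denominator df 56 instead of 57.

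| r | Mean of both scans | Change | Post-only | ANCOVA |
|---|---|---|---|---|
| 0 | 0.465 | 0.465 | 0.776 | 0.775 |
| 0.2 | 0.397 | 0.560 | 0.776 | 0.793 |
| 0.3 | 0.369 | 0.621 | 0.776 | 0.815 |
| 0.5 | 0.325 | 0.776 | 0.776 | 0.887 |
| 0.7 | 0.291 | 0.946 | 0.776 | 0.973 |

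Simulated ANCOVA power is slightly lower (0.807, 0.880, 0.971 at r = 0.3, 0.5, 0.7), because chance baseline imbalance costs a little. Simulated type I error at r from 0 to 0.9 is 0.049 to 0.051 for change scores and 0.050 to 0.051 for ANCOVA.

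**The case against.** The protocol never says that the scans will be treated as independent. The name two-way ANOVA is also used for the mixed, repeated-measures form, whose interaction holds the 5% level. The aim in 11.1 is change, which is that interaction, and excluding anyone without both scans fits a paired analysis. The phrase about averages in 11.3.2 need not mean an average over both time points, since the next sentence looks at the post-intervention mean. Section 11.3 defers detail to an analysis plan that may already name the model.

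Most of this stands. A reader might infer that the plan ignores pairing and so has an inflated error rate, or that it dilutes the effect by averaging baseline into the outcome. The text establishes neither; both are consequences of readings it leaves open. Nor is ANCOVA the only valid remedy: a model with a participant effect, read at group-by-time, also has the correct error rate.

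Deferral to the analysis plan does not remove the point. Sections 11.1 and 11.3.2 already state a test and a decision rule, and they do not describe the same comparison. An analysis plan could resolve this only by choosing between protocol statements, after which the protocol should agree with it.

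**Conclusion.** The point holds as a failure to fix the model and the tested effect, together with an available gain in efficiency. It is not a demonstrated error-rate fault. A wrong type I error arises only if the ANOVA is unpaired, and dilution only if the group main effect over both scans is tested.

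On the favourable reading, a repeated-measures interaction, the test is valid but falls short of 80% power at r = 0.3 and 0.5, whereas ANCOVA exceeds it at both. The advantage over change scores is about 19, 11 and 3 percentage points at r = 0.3, 0.5 and 0.7 (0.815 − 0.621, 0.887 − 0.776, 0.973 − 0.946).

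The gain rests on an assumed r. At r = 0, ANCOVA gains nothing over post-only, and at r = 0.2 or below 60 subjects remain short of 80%. All power figures also assume that 0.4 is Cohen's f on the post-intervention scale and that all 60 are analysed.

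ANCOVA does not correct the numerator df of 1 behind the 52, nor deal with two main endpoints each judged at 0.05. Those are separate matters.

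**What to change.** In 11.1 and 11.3.2, name one primary model for each index: ANCOVA of the post-intervention value on group, with the pre-intervention value of the same index as covariate, plus any stratification factor actually used (section 6.2 makes stratification conditional on a preliminary experiment). State that the decisive p-value is the group effect in this model, and apply the decision rule to the adjusted group means. Remove the two-way ANOVA wording, or keep it only as a supporting analysis with a participant effect, read at group-by-time.

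The cost is a wording change in the protocol, matched in the analysis plan, and one degree of freedom per covariate (more for a factor with over two levels). No extra scans or subjects are needed. The change should be made before any outcome data are examined.

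### The stated 52 subjects for 80% power matches an F test with 1 numerator degree of freedom, but comparing change between three groups takes 2; section 11.1 needs restating

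*Protocol*

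**What the plan says.** All of the sample-size basis is in Protocol section 11.1, whose stated aim is to look at before/after change across three groups.

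- Analysis: "Specifically, a two-way analysis of variance will be used for statistical analysis".
- Design inputs: "The number of levels is 1 (before or after the intervention) and the number of groups is 3".
- Numerical inputs: "Assuming an effect size of 0.4, a significance level of less than 5% and a power of 0.8". Section 11.3 adds: "The significance level of the test is set at two-sided 0.05".
- Result: "the sample size for each group will be calculated to be 52 participants in total". The sentence mixes per-group and total wording; 52 can only be a total, since the target is 60.
- Step up to 60: "Assuming that there will be a certain number of subjects who declare that they cannot consent to randomisation and who meet the exclusion criteria", the aim becomes 60. No rate is given.
- Target, section 10: "Target number of patients enrolled: 60 (20 in group M, 20 in group P and 20 in group C").

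Section 11.3.2 tests the primary endpoints by comparing the mean of each index across the three groups. Section 11.2 leaves out of the analysis anyone who does not complete the intervention or lacks an image before or after it.

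**The concern.** Before/after is a two-level factor; 1 is its degrees of freedom, not its number of levels. If that 1 was carried into the calculation as the numerator degrees of freedom, the 52 belongs to the overall time effect (or to a two-group contrast). Neither is the comparison used to judge the interventions. Whether groups differ in change is the group-by-time term, with (3 − 1)(2 − 1) = 2 degrees of freedom. A comparison of three group means also has 3 − 1 = 2.

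At stake is how the result is read. As written, 52 analysed subjects suffice for 80% power and 60 leaves 8 to spare. If 52 is too low for the test in section 11.3.2, a null result would be credited with more power, and the trial with more slack, than the stated inputs support.

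**Working it through.** **Inputs.** Effect size 0.4, significance level 0.05, power 0.80, 3 groups (sections 11.1 and 11.3); target 60 as 20/20/20 (section 10). Assumption: 0.4 is Cohen's f, since section 11.1 does not name the measure.

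**Formula.** Power is the probability that a noncentral F variable with df1 and df2 = N − 3 degrees of freedom and noncentrality λ = f²N exceeds the 5% critical value of the central F. With f = 0.4, λ = 0.16 N.

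**Step 1: the plan's own figure (df1 = 1).**

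| N | λ | Power |
|---|---|---|
| 51 | 8.16 | 0.799 |
| 52 | 8.32 | 0.807 |

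The smallest N reaching 0.80 is 52, an exact match. Counting 2 or 6 cells instead of 3 in df2 also gives 52.

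**Step 2: same inputs, df1 = 2.**

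| N | λ | Power |
|---|---|---|
| 52 | 8.32 | 0.707 |
| 54 | 8.64 | 0.726 |
| 60 | 9.60 | 0.776 |
| 63 | 10.08 | 0.798 |
| 64 | 10.24 | 0.805 |
| 66 | 10.56 | 0.818 |

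So 80% needs 64, or 66 with equal groups. The shortfall is 80 − 70.7 = 9.3 points at 52 and 80 − 77.6 = 2.4 points at 60. The smallest f detectable with 80% power is 0.444 at 52 and 0.411 at 60. The row for 54 is an assumed loss of 6; the protocol gives no loss rate.

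**Step 3: can another calculation explain 52?**

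- df1 = 2 at a 10% level gives 51, and contradicts the stated 5%.
- A repeated-measures group-by-time interaction with two measurements (λ = 2f²N/(1 − ρ), df1 = 2) gives 34 at ρ = 0 and 19 at ρ = 0.5.
- A repeated-measures between-group test (λ = 2f²N/(1 + ρ), df1 = 2) gives 49 at ρ = 0.5 and 56 at ρ = 0.75, so it passes through 52 at about ρ = 0.6. It needs a correlation that the protocol does not state, uses two measurements where section 11.1 says 1, and tests the average over both times, not change.

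Only the calculation with 1 degree of freedom gives 52 from the stated inputs alone.

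**Step 4: from 52 to 60.** Section 4.1 makes written consent a condition of entry, and section 6.1 puts an eligibility review before registration. Someone who refuses randomisation should therefore not be one of the 20/20/20 allocated. Ineligibility differs: section 11.3.1 plans to count enrolled subjects who later prove ineligible, so some could fall within the 60. Neither has a rate, and section 11.1 does not mention the exclusions of section 11.2.

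**The case against.** **The power may be ample.** Section 11.1 does not say which term or scale the 0.4 belongs to. As the interaction effect of a repeated-measures analysis at ρ = 0, it would give about 95% power at 52 and 98% at 60. If 0.4 is scaled to the standard deviation at one time point and change is analysed, power at 60 is 46.5% at ρ = 0, 77.6% at ρ = 0.5 and 94.6% at ρ = 0.7 (all correlations assumed). This stands: a reader might infer that the trial is underpowered at 60, and the document does not establish that. It does not rescue the 52, because the interaction formula asks for about 34 or fewer.

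**One degree of freedom is never mentioned.** True. It is inferred from the exact match and from the figure of 1 for levels, in a translated text. The inference is strong but remains one.

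**The 60 does contain some margin.** A reader might conclude that nobody covered by the stated reasons can be among the 60. Section 11.3.1 contradicts that for ineligibility found late. The criticism holds for refusals, for the missing rate and for the silence on section 11.2.

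**The effect is small.** At the actual target the shortfall on the stated inputs is 2.4 points. With one session of about 10 minutes and imaging before and immediately after, few losses are likely. This stands and limits the severity.

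**Conclusion.** The point holds in a limited form. Section 11.1 misstates the number of levels, and its 52 for 80% power is wrong as calculated for a three-group comparison of change. With 0.4 as Cohen's f for that comparison, on change scores if change is tested, 52 gives 70.7%, 60 gives 77.6%, and 80% takes 64 (66 balanced).

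The size rests on that reading of the 0.4 and on the inferred single degree of freedom. It does not show that the trial as run would miss 80%: that depends on the effect-size scale and the pre/post correlation, neither of which is stated. The allowance of 8 is poorly justified rather than absent. This should be fixed, but at the target of 60 it is not a serious threat to the trial.

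**What to change.** Keep 60 and rewrite section 11.1:

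1. State 2 time levels by 3 groups, name the tested term and give its 2 numerator degrees of freedom.
2. Say what the 0.4 is: the measure, the standard deviation it is scaled to, and any pre/post correlation used. The figures in the next item are valid only on the scale used here.
3. Either replace 52 with 64 (66 balanced) as the number for 80% power and acknowledge that 60 is below it, or state that 60 analysed gives about 78% power for f = 0.4 (80% for f = 0.41).
4. Remove refusal of randomisation as a reason for 60. Say that any allowance is for subjects found ineligible after enrolment or excluded under section 11.2, and that power falls with such losses, for example to about 73% if 54 are analysed (an assumed loss).

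The cost is rewording, with ethics committee approval of the change under section 17, and a slightly less favourable power statement. No subjects, visits or measurements are added.

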## 11.2 Statistical analysis methods

Analyses of the effectiveness of interventions will be carried out in the Full Analysis Set (FAS).

FAS

The FAS is the analytic population consisting of subjects who do not meet any of the following criteria

a) If you are unable to complete the intervention for any reason

b) If ultrasound imaging was not available before or after the intervention

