## 5.2 Outline of the study

Massage and exercise group (group M), physical stimulation group (group P)

Register

Eligibility check

Obtaining consent

Intervention period

Pre-observation period

Tracking period

One single intervention

None in particular

2 weeks

End of experiment

End of intervention

Start of intervention

Control group (Group C)

The pre-observation period, intervention period and follow-up period all follow the same process as above.

No intervention, but a total of two ultrasound imaging sessions with a 10-minute pause for comparison with the intervention group.

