## 5.3 How interventions are delivered

Exercise stimulus group; 1/3 of participants

　A massage/manual therapy, quantified in a preliminary experiment, will be performed on the infrapatellar fat pad for approximately 10 minutes. Specifically, a pressure sensor will be used to measure the finger pressure during the manual approach of the interventionist to ensure that a constant pressure is applied.

[figure not shown]
　　　　　
[figure not shown]

Physical stimulus group; 1/3 of participants

　The infrapatellar fat pad body is subjected to vibration stimulation quantified in the preliminary experiment for approximately 10 minutes. The frequency of the vibration stimulation is quantified by using a device that can quantify the frequency of the vibration stimulation, so that the vibration stimulation is applied at a constant frequency.

Equipment to be used: Slieve MD01 handy massager.

The interventions in the above two groups will be carried out by a researcher ([name]) who has been carefully trained beforehand.

Control group; 1/3 of participants

　No specific interventions will be made, but there will be a 10-minute waiting period.

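### The Full Analysis Set in section 11.2 is a completer set: it drops randomised subjects who do not finish the intervention, even when both scans exist

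*Protocol*

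**What the plan says.** Section 11.2 names one population for effectiveness, the Full Analysis Set, and defines it by exclusion: "The FAS is the analytic population consisting of subjects who do not meet any of the following criteria". Two criteria follow:

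- "a) If you are unable to complete the intervention for any reason"
- "b) If ultrasound imaging was not available before or after the intervention"

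Section 11.3.1 has non-completers counted by reason, and analysed numbers reported by group. It does not return non-completers to any analysis, and no other analysis set is named.

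Section 5.3 describes what there is to complete. In group M, manual therapy "will be performed on the infrapatellar fat pad for approximately 10 minutes". In group P, the fat pad "is subjected to vibration stimulation quantified in the preliminary experiment for approximately 10 minutes". For group C: "No specific interventions will be made, but there will be a 10-minute waiting period". Section 5.2 adds, for group C: "No intervention, but a total of two ultrasound imaging sessions with a 10-minute pause for comparison with the intervention group".

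Under section 11.3.2 an intervention may be judged useful if p is below 0.05 and the mean after the intervention is higher in M or P than in C. Sections 0 and 5.1 describe the trial as unblinded; section 7.2 has the imaging done by a blinded researcher.

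**The concern.** Completion is known only after randomisation and depends on the treatment received. Selecting on it gives up the protection of randomisation for whoever is removed. A reader who sees the label Full Analysis Set will expect something close to all randomised subjects, analysed as allocated. What section 11.2 defines is nearer to a per-protocol set.

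The first criterion is also uneven across arms. Stopping because pressure or vibration is uncomfortable can happen only in M or P. If stopping is related to the ultrasound outcome, M minus C and P minus C are shifted, and those are the comparisons on which the judgement of usefulness rests. With 20 per arm, two exclusions are 10% of an arm. Blinded imaging does not help, because the exclusion arises during treatment and not at the reading of the image.

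**Working it through.** **Step 1. What each criterion removes.**

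| Completed intervention | Both scans available | Removed by |
|---|---|---|
| Yes | Yes | neither |
| Yes | No | (b) |
| No | No | (a) and (b) |
| No | Yes | (a) only |

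Only the last row is due to criterion (a) alone: randomised subjects with usable before and after data. That row need not be empty, since the second scan follows immediately on one session of about 10 minutes (sections 0, 5.2, 5.3 and 8).

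**Step 2. Which arms.** Criterion (a) has a real counterpart in M and P. In C there is only the wait. Criterion (b) covers all three arms: a control who leaves during the wait, or lacks a scan, is removed under it.

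**Step 3. Possible size.** The plan gives no figure for this. Section 11.1 raises 52 to 60, a margin of 8/60 = 13.3%, but attributes it to refusal of randomisation and to ineligibility, so it supplies no non-completion rate.

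Input from the plan: 20 per arm (section 10); alpha two-sided 0.05 (section 11.3); the decision rule of section 11.3.2, taken here as a three-group F test with p<0.05 and the M mean above the C mean. Assumptions: one normally distributed outcome per subject, SD 1 in every arm, no true effect, k subjects removed from M and none from P or C.

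*Worst case: the removed subjects are exactly the lowest in M.* The expected lowest three of 20 standard normal values are about -1.87, -1.41 and -1.13. The arm mean rises by minus the sum of the removed values divided by the number left:

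- k = 1: 1.87/19 = 0.10 SD
- k = 2: (1.87 + 1.41)/18 = 3.28/18 = 0.18 SD
- k = 3: (1.87 + 1.41 + 1.13)/17 = 4.41/17 = 0.26 SD

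*Partial dependence.* If the tendency to stop has correlation r with a low outcome, the shift is r times the worst case. For k = 2: 0.3 × 0.182 = 0.055 SD, and 0.5 × 0.182 = 0.091 SD.

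*Chance of p<0.05 with M above C.* Found by simulating null trials; where two values are given, they are the spread between simulation runs.

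| Removed from M | Relation to outcome (assumed) | Shift in M minus C | Chance |
|---|---|---|---|
| 0 | none | 0 | 2.5% |
| 2 | unrelated | 0 | about 2.5% |
| 2 | correlation 0.3 | about 0.05 SD | 3.3% to 3.4% |
| 2 | correlation 0.5 | about 0.09 SD | 4.2% to 4.4% |
| 2 | exactly the lowest two | 0.18 SD | 8.0% |
| 1 | exactly the lowest | 0.10 SD | 4.7% to 4.8% |
| 3 | exactly the lowest three | 0.26 SD | 11.7% to 12.1% |

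By symmetry, if those who stop are the highest in M, the shifts have the opposite sign.

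**The case against.** The strongest reply is that little will happen in practice. Subjects are healthy students, there is one session of about 10 minutes, section 9 expects no adverse events, and the second scan is immediate. Non-completers should be few, and the counts by reason and by group in section 11.3.1 would show any imbalance. This stands, and it limits the severity. It does not make the definition right, because counting those removed does not put them back into the comparison.

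Three stronger readings are tempting, and the documents do not support them:

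- *That exclusions from the set fall only on M and P.* Criterion (b) applies to every arm, and group C has two scans and a wait that can be left unfinished. The one-sidedness belongs to criterion (a) alone, and there it is a matter of practice.
- *That the bias favours the interventions.* Nothing links early stopping to a poor ultrasound response. The endpoints are tissue flexibility and gliding, not comfort. The shift could be up, down or nil.
- *That 0.18 SD and 8.0% are what to expect.* They require 10% of one arm to stop and those two subjects to be exactly the lowest.

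It can also be said that the statistical analysis plan, not at hand, may add another set. It may, so the absence of an as-randomised set is a statement about the protocol only. But section 11.2 does not defer the definition; it states one, and a plan that follows it would inherit it.

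Finally, the remedy below still requires both images, so it is not a strict intention-to-treat set. That is fair. It recovers only subjects who stopped early and were scanned, which are the ones now lost without need.

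**Conclusion.** Wrong as written; should be fixed, but not a defect that by itself invalidates the trial. The set called the Full Analysis Set is a completer set, and the protocol offers no as-randomised alternative. This follows from the text of section 11.2 and needs no assumption.

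The effect on the result does rest on assumptions: how many subjects stop early, in which arm, and how stopping relates to the outcome. With two removed from M the range runs from no shift to 0.18 SD in size, and moderate dependence gives about 0.05 to 0.09 SD. Neither the number nor the direction can be taken from the documents, and in a single short session the realised bias is probably small.

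**What to change.** In section 11.2:

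1. Delete criterion (a).
2. Define the Full Analysis Set as all randomised subjects with before and after images, analysed in the allocated group whether or not the intervention was completed.
3. State that the already scheduled after image is also taken in subjects who stop early.
4. Keep the present definition as a per-protocol set for a sensitivity analysis.

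Make the change before outcome data are examined, since redefining the population later would itself be open to challenge.

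The cost is a rewording and one additional analysis; no extra visit or scan is needed. The estimated effect may be slightly diluted by incompletely treated subjects, and the per-protocol analysis will show by how much.
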